### Study retention

The follow-up observation study protocol is as follows:
After 8 weeks of treatment, the patients will enter the follow-up period. Patients who benefited from the treatment will be maintained on the treatment but at a reduced treatment frequency, with treatment not exceeding 2 months.During the follow-up period, patients will be monitored using mobile application software, telephone, SMS text or other methods to communicate on a regular basis. Additionally, patient health management, regular health education and life guidance will be provided. A record of the patient’s medications will be monitored. Patients who benefited from treatment and were still in relapse at the 6-month follow-up will be further evaluated for long-term efficacy. The patient’s recovery will be monitored using application software or telephone feedback information every 4 weeks. Changes in target lesion area will be monitored via application every 2 weeks. Patients will be required to visit the clinic every 3 months to monitor symptoms and signs, conditions, PASI score, skin DLQI and TCM syndrome efficacy score.If the patient relapses, the follow-up will terminate. Patients will then be required to seek medical advice and treatment promptly.

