### Study outcomes

#### Primary outcomes

The primary outcomes will include the relapse rate and PASI score of the target lesions [34, 35]. The relapse rate will be defined as the recurrence of skin lesions after recovery that reaches 50% of the original PASI score, based on the American Academy of Dermatology Expert Association.

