### Data collection

Data will be collected using a CRF. The research medical records and case reports will be completed by the researcher for all enrolled patients. Completed case reports will be reviewed by the clinical monitor, and then handed over to the data administrator for data entry and management.

The following patient information will be collected: general information (including name, gender, birth date, marriage status, time of disease diagnosis and onset), complaint and symptoms, family history, use of pharmaceutical drugs, physical examination, skin lesions, additional symptoms evaluated using the TCM scale, target lesion imaging and scoring, and the DLQI questionnaire. Information regarding adverse events will be recorded during the procedure and on follow-up. Images of skin lesions, PASI scores, TCM syndrome assessment, DLQI, etc. will be performed at patient enrollment and after 2, 4, 6 and 8 weeks of treatment and during the follow-up period (12 and 24 weeks after intervention is completed).

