### Statistical analysis

Statistical analysis will be performed using the SAS (version 9.4) software by a statistician who is blinded to the patient grouping. Continuous variables will be presented as mean ± standard deviation (normally distributed data) or medians and ranges (non-normally distributed data). Frequencies and percentages will be used for count data.

Additional statistical tests will be performed using a bilateral differential test, with a *p* value <0.05 considered as statistically significant. For the primary outcome of relapse incidence, survival analysis will be used. Measurement data will be analyzed using *t* test and rank sum test. Count data will be analyzed using chi-square test and Fisher’s exact test, while grade data will be analyzed using Ridit and CMH. Overall evaluation index and the main efficacy indexes will simultaneously be analyzed using per-protocol and intention-to-treat analysis, while multicenter count data will be analyzed using the CMH method. Variance analysis will be performed for measurement data. For confounding factors that are difficult to predict or that are uncontrolled before treatment, i.e., imbalance between the groups before treatment, the least squares mean of covariance analysis and its 95% confidence limit or logistic will be used as covariates. Regression will be used to determine differences in efficacy between the groups and to eliminate the effects of these confounding factors on efficacy.

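### Relapse times are known only to within 12 weeks, and in-clinic maintenance could date relapses earlier in the fire needle and moxibustion arms; relapse should be analysed in common intervals in every arm

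*Protocol article*

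**What the plan says.** - **Event.** Primary outcomes (Protocol article) defines relapse as "recurrence of skin lesions after recovery that reaches 50% of the original PASI score", so a PASI score is needed to establish it.
- **PASI schedule.** Data collection lists PASI at enrolment, during treatment and "during the follow-up period (12 and 24 weeks after intervention is completed". Study retention agrees: "Patients will be required to visit the clinic every 3 months".
- **Contacts between visits.** Study retention adds "Changes in target lesion area will be monitored via application every 2 weeks", and recovery "monitored using application software or telephone feedback information every 4 weeks". Neither is limited to an arm, and the app check records lesion area, not PASI.
- **Maintenance.** Responders are "maintained on the treatment but at a reduced treatment frequency, with treatment not exceeding 2 months". The reduced frequency is not given. Fire needling and Moxibustion both place treatment in a dermatology clinic; Control group describes an ointment used morning and evening.
- **End of observation.** Study retention stops follow-up once a patient relapses. Blinding says that only the statisticians are blinded.
- **Analysis.** "For the primary outcome of relapse incidence, survival analysis will be used". No method is named. The relapse interval of the target lesion is a secondary outcome.

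The article does not say which contact dates a relapse, whether PASI is scored at maintenance sessions, or whether a change seen between visits needs a PASI before it counts.

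**The concern.** Two features combine. First, with PASI at only two follow-up points, a relapse time is interval-censored: it lies somewhere in weeks 0–12 or 12–24. Second, the chance of noticing a relapse inside the first interval may differ by arm. A patient continuing fire needling or moxibustion presumably meets treating staff in clinic during the first 2 months; a patient continuing ointment may not. Relapse is counted only after recovery, so the patients at risk overlap heavily with the responders who are kept on treatment.

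If a relapse seen at a maintenance session is dated that day, while one in the ointment arm waits for week 12, identical disease courses give different event times. A log-rank test, hazard ratio or median time to relapse would then partly measure how often each arm is looked at. Because follow-up ends at relapse, a call made between visits without PASI could not be checked afterwards.

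**Working it through.** **1. The plan's own figure.** Inputs from Sample size estimation: 12-week relapse 38% (A1) and 67% (B), two-sided 0.05, power 0.80, A1:B = 2:1, pooled Z test.

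n_B = [1.96·√(p̄(1−p̄)·1.5) + 0.8416·√(0.67·0.33 + 0.38·0.62/2)]² / 0.29², with p̄ = (0.67 + 2·0.38)/3 = 0.4767

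= (1.199 + 0.490)² / 0.0841 = 33.9, so 34 in B and 68 in A1. The stated 33 and 66 give 78.9% power. The stated figure is reproduced to within 2 patients, and 66 versus 33 is used below.

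**2. Underlying times.** Assuming exponential relapse times, λ = −ln(1 − p)/12:
- 38%: λ = 0.0398 per week, median ln2/λ = 17.4 weeks.
- 67%: λ = 0.0924 per week, median 7.5 weeks.

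Dated only at visits, those medians become 24 and 12 weeks.

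**3. How unequal looks act.** Suppose both arms truly relapse at 67% by week 12. By week 8 the cumulative rate is 1 − exp(−8·0.0924) = 52%. With maintenance looks, about 66·0.52 = 34 A1 relapses carry dates in weeks 1–8; none of B's 33·0.52 = 17 do. At week 12 both arms stand at 67% (44 of 66 and 22 of 33). The 12-week proportion is equal, but the dated curves are not.

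**4. Simulation.** Log-rank test, 66 versus 33, exponential times, all patients at risk from end of treatment, each relapse dated at the first look after it occurs, 3,000 trials per scenario (simulation error about 0.4 points near 5%). The look frequencies at maintenance are assumptions.

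| Looks that date relapse | False positives at 38 / 50 / 67% true 12-week relapse | Power, 38% vs 67% |
|---|---|---|
| Weeks 12 and 24 only, both arms | 4.7 / 4.7 / 5.1% | 92.5% |
| A1 weekly in weeks 0–8; B at 12 and 24 | 6.6 / 15.8 / 60.3% | 47% |
| A1 2-weekly in weeks 0–8; B at 12 and 24 | 7.0 / 15.3 / 58.1% | 49% |
| Half of A1 2-weekly in weeks 0–8; B at 12 and 24 | 4.9 / 7.1 / 20.1% | 72% |
| A1 weekly in weeks 0–8, plus 4-weekly contact in both arms | 5.4 / 5.2 / 6.2% | 88% |
| A1 weekly in weeks 0–8, plus 2-weekly app check in both arms | 4.5 / 5.7 / 5.3% | 92% |

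Repeat runs agree to within a few points (56–60% for the largest false-positive rate, 47–50% for the lowest power). Where extra looks fall on all of A1 and B is seen only at 12 and 24 weeks, nearly all false positives make A1 look worse. With exact dates power would be about 94%, so the common 12- and 24-week grid gives up about 2 points.

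**The case against.** The strongest reply is that the bias needs two rules at once. If only a scheduled PASI can establish relapse, maintenance contacts cannot date it, all arms share the 12- and 24-week grid, and the error rate is about 5%. If contacts between visits can date relapse, the app and telephone contacts, the same in all arms, count too and the distortion nearly disappears. This stands as a limit on size. It does not settle the matter, because the article does not say which rule applies.

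Other points also stand. No PASI is scheduled at maintenance sessions and their frequency is not given. Maintenance is offered to responders in every arm, and ointment patients return used tubes after visits, so home use with little staff contact is inferred. The scenario with 67% in both arms is far from the 38% planned for A1, where the false-positive rate is about 7%. The article names no log-rank test, and an interval-censored method may sit in an analysis plan that is not shown. The 12-week proportion behind the sample size does not depend on when within 12 weeks a relapse is found, provided it is recorded or still present at week 12.

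Two stronger readings are tempting. A reader might infer that app monitoring dates relapses earlier in some arms; Study retention applies it without restriction by arm, so it is not an arm-specific source. A reader might also infer that the design favours fire needling; unequal maintenance looks act against it.

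**Conclusion.** The point holds in a limited form. What the article fixes is enough to say that relapse times are interval-censored to 12 weeks, and that maintenance could lead to earlier detection in the fire needle and moxibustion arms than in the ointment arm. If relapses are dated when found at those contacts, the primary comparison tilts against the two clinic-based arms, and the likelier harm is lost power or a falsely worse result.

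The size is conditional. Losing nearly half the power (92% to 47–50%) is a worst case in which every A1 patient gets extra looks and B gets none. It shrinks to 72% with half of A1 seen, and to little or nothing if contacts shared by all arms also date relapse. These figures rest on exponential times, assumed visit frequencies, all 66 and 33 patients at risk, and a log-rank test. The documents do not show that the bias will occur. They do leave open a dependence on contact frequency that the analysis can remove cheaply, so the change should be made.

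**What to change.** In Statistical analysis:
- Analyse relapse in the common intervals 0–12 and 12–24 weeks after treatment in all three arms, using a grouped-time (interval-censored) proportional hazards model with complementary log-log link and terms for arm, interval and centre.
- Assign any relapse found between visits to the interval in which it falls.
- Report the relapse interval of the target lesion as interval-censored, without exact-date medians.

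In Primary outcomes and Study retention, state one source and one PASI basis for calling a relapse, the same in every arm, and say what role app-reported lesion area has in it.

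The first interval matches the 12-week endpoint behind the sample size. In the simulations the common grid keeps type I error near 5% and power near 92%. The cost is some wording, one model, about 2 points of power against exact dates that scheduled PASI cannot supply, and coarser timing of relapse. Holding every arm to the same PASI basis is also a small matter of trial conduct, so it should be settled before the data are collected where that is still possible.

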### Data management

A database will be established using EpiData 3.1 software (EpiData Association, Denmark). For the data entry and management, medical statisticians will appoint data administrators. In order to ensure the accuracy of the data, two data entry technicians will independently enter and verify the data twice. Proper training will be provided to the technicians before data entry.

After completion of the data entry, reports on the consistency of the database will be generated. Any inconsistencies found in the database will be verified and corrected.

SAS (version 9.4) software will be used for data verification. Verification will include logical errors, missing data and extreme data. Afterwards, a data verification report will be generated to be sent to the clinical monitor for verification. Any inaccuracies will be checked by the data administrator, who will perform data modification, confirmation, and entry based on the researcher’s response. After both parties are satisfied with the final data version, it will be locked for statistical analysis.

### Statistical analysis

Statistical analysis will be performed using the SAS (version 9.4) software by a statistician who is blinded to the patient grouping. Continuous variables will be presented as mean ± standard deviation (normally distributed data) or medians and ranges (non-normally distributed data). Frequencies and percentages will be used for count data.

Additional statistical tests will be performed using a bilateral differential test, with a *p* value <0.05 considered as statistically significant. For the primary outcome of relapse incidence, survival analysis will be used. Measurement data will be analyzed using *t* test and rank sum test. Count data will be analyzed using chi-square test and Fisher’s exact test, while grade data will be analyzed using Ridit and CMH. Overall evaluation index and the main efficacy indexes will simultaneously be analyzed using per-protocol and intention-to-treat analysis, while multicenter count data will be analyzed using the CMH method. Variance analysis will be performed for measurement data. For confounding factors that are difficult to predict or that are uncontrolled before treatment, i.e., imbalance between the groups before treatment, the least squares mean of covariance analysis and its 95% confidence limit or logistic will be used as covariates. Regression will be used to determine differences in efficacy between the groups and to eliminate the effects of these confounding factors on efficacy.

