### Randomization and allocation concealment

Sequence generation will be performed using the PROC PLAN process in SAS 9.4 software (Beijing Hospital of TCM Version; Order Number: 9C1XJD). The numbers for each center will be randomly assigned. The proportion of randomization will be set at 2:1:1 for Group A1 (fire needle combined with acupuncture) to Group A2 (moxibustion) to Group B (calcipotriol). A statistician will then encode the grouping results and seal in an envelope, which will be handed to patients based on their enrollment order. Outcome assessment and statistical analysis will be performed by independent statisticians from the Beijing Institute of Traditional Chinese Medicine who are blinded to the group assignments.

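### Baseline adjustment of target-lesion PASI depends on an undefined pre-treatment imbalance; one baseline-adjusted model should be named in advance and always fitted

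*Protocol article*

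**What the plan says.** The Primary outcomes section states: "The primary outcomes will include the relapse rate and PASI score of the target lesions". PASI is therefore a primary outcome and falls under the rules for measurement data.

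The Statistical analysis section gives those rules in three places:

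- "Measurement data will be analyzed using *t* test and rank sum test".
- "Variance analysis will be performed for measurement data", with no factors named.
- An adjustment clause that opens "For confounding factors that are difficult to predict or that are uncontrolled before treatment, i.e., imbalance between the groups before treatment" and continues "the least squares mean of covariance analysis and its 95% confidence limit or logistic will be used as covariates". The wording is loose, since a least squares mean is a result of a model and not a covariate. The evident meaning is that covariance analysis or logistic regression is used when groups differ at baseline.

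Nothing says how large an imbalance must be, which variables are examined, or which of the named methods is primary for PASI.

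On centre, the same section says "multicenter count data will be analyzed using the CMH method", without any condition. For relapse it says "For the primary outcome of relapse incidence, survival analysis will be used". The Randomization and allocation concealment section says "The numbers for each center will be randomly assigned".

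The Data collection section has PASI scored at enrolment, at weeks 2, 4, 6 and 8 of treatment, and at 12 and 24 weeks after treatment. Baseline PASI is thus planned for every patient.

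**The concern.** Whether baseline PASI belongs in the model does not depend on whether the arms happen to differ on it. If it predicts later PASI, including it sharpens the comparison even when the arms are balanced. Under proper randomisation, a significance test of baseline PASI is positive in only 5% of trials, so a rule of that kind leaves the gain unused in nearly all of them.

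The rule is also open-ended. With three unadjusted methods, one conditional adjusted method and no threshold, the PASI analysis is settled only after data are in hand. Nothing in the text stops the adjusted and unadjusted results from both being viewed before one is called primary. Treating patients, researchers and outcome evaluators are unblinded (Blinding section), so a fixed primary model is one of the few protections left for this outcome. Blinding the statistician helps, but a p value can be seen without knowing the group labels.

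**Working it through.** **The plan's own figure.** The Sample size estimation section uses relapse of 38% against 67%, two-sided 0.05, power 0.8, pooled variance and a 2:1 ratio. The pooled proportion is (0.67 + 2×0.38)/3 = 0.477. Then

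n(B) = [1.96·√(0.477·0.523·1.5) + 0.842·√(0.67·0.33 + 0.38·0.62/2)]² / 0.29² = 33.9, or 34 in B and 68 in A1.

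The plan states 33 and 66, which give power 0.789. That is agreement for practical purposes. The relapse sample size is not affected by this point, and the document gives no power figure for PASI.

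**Inputs for PASI.** Arm sizes of 66 and 33, or 80 and 40, come from the same section. The correlation ρ between baseline and outcome PASI is not given; 0.3 to 0.7 is assumed. Scores are in SD units.

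**Reference effect.** The difference with 80% power for an unadjusted comparison of final scores is

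d = √(1/33 + 1/66) × (1.960 + 0.842) = 0.2132 × 2.802 = 0.597 SD (0.543 SD with 40 and 80).

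**Always adjusting.** The residual SD becomes √(1−ρ²), and power = Φ(2.802/√(1−ρ²) − 1.960). For comparison, change from baseline has SD √(2(1−ρ)).

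| ρ | Variance reduction ρ² | Detectable effect, 66/33 | Power, final score unadjusted | Power, change score | Power, baseline-adjusted |
|---|---|---|---|---|---|
| 0.3 | 9% | 0.57 SD | 80% | 65.8% | 83.6% |
| 0.5 | 25% | 0.52 SD | 80% | 80.0% | 89.9% |
| 0.7 | 49% | 0.43 SD | 80% | 95.1% | 97.5% |

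**Adjusting only on a trigger.** A simulation with normal data, 33 against 66 and 40,000 runs per setting assumed that adjustment is made when the baseline difference has p<0.05. That threshold is an assumption, because the plan gives none.

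| ρ | Power: t test | Power: trigger | Power: always | Type I: trigger | Type I: smaller p of the two |
|---|---|---|---|---|---|
| 0.3 | 0.792 | 0.794 | 0.823 | 0.049 | 0.065 |
| 0.5 | 0.794 | 0.805 | 0.891 | 0.043 | 0.072 |
| 0.7 | 0.795 | 0.813 | 0.972 | 0.035 | 0.082 |

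The share of the gain that the trigger recovers is (0.7944−0.7922)/(0.8228−0.7922) = 7% at ρ = 0.3, 11% at 0.5 and 10% at 0.7. The simulation error on a rate of 0.05 is √(0.05·0.95/40,000) = 0.001. Results at 40 against 80 are nearly the same: trigger power 0.797, 0.807, 0.813; always 0.828, 0.894, 0.973; smaller-p type I error 0.063, 0.074, 0.080.

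**Centre.** No between-centre variance is given, so the gain from a centre term cannot be computed.

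**The case against.** **This is a condensed article, and detail belongs in the analysis plan.** That is fair for silence, but the imbalance trigger is a rule the article states. It stands as a finding.

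**A reader might infer that centre adjustment also waits for an imbalance, or that centre is left out of the relapse and PASI analyses.** The text does not support this. The Cochran–Mantel–Haenszel method for multicentre count data is unconditional. The variance analysis, named immediately afterwards, may include centre as a factor, and the survival analysis may be stratified. These terms are unstated, which in an article of this kind is not the same as absent. The sentence about numbers for each centre suggests stratified randomisation but does not say so outright.

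**A reader might infer that the plan inflates the false-positive rate.** If the arms differ at baseline by 1.5 standard errors and no adjustment is made, the unadjusted test rejects a true null in 8.2% of trials at ρ = 0.5 and 10.1% at ρ = 0.7. Those figures are correct but conditional on a chosen imbalance and an assumed significance threshold; a difference of that size might well be judged an imbalance and adjusted for. With perfect balance the same calculation gives about 2.4% and 0.6%. Averaged over randomisations the unadjusted test holds 5%, and the simulated trigger is slightly conservative. The 0.065 to 0.082 arises only if the better of two results is picked. The plan does not say this will happen; it only fails to prevent it.

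**The efficiency loss rests on assumptions.** This stands. The correlation is assumed, the article does not say whether final or change scores are compared, and a looser trigger would recover more. If change scores are used and ρ is 0.7, adjustment adds only about 2 points of power (95.1% to 97.5%).

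**Conclusion.** The point holds for baseline adjustment of PASI. The stated rule makes the model for a primary outcome depend on an undefined look at baseline data and gives up most of what baseline PASI could contribute. Against an unadjusted comparison of final scores with 80% power, the loss is about 4, 10 or 17 points at assumed correlations of 0.3, 0.5 or 0.7. Against change scores it is about 18, 10 or 2 points. A trigger at p<0.05 changes this little. The harm is lost precision and an open choice of model, not an inflated average error rate. It does not touch the relapse sample size. It is worth correcting because the remedy is nearly free.

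**What to change.** In the Statistical analysis section:

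1. Delete the clause that makes adjustment depend on pre-treatment imbalance.
2. Name one primary PASI model, fitted whatever the baseline looks like: target-lesion PASI at the sponsor's chosen primary time point, with arm, baseline target-lesion PASI and centre. Report adjusted differences between arms with 95% confidence intervals.
3. Keep the unadjusted t test and the rank sum test as sensitivity analyses, labelled as such.
4. Carry the centre factor, already planned for count data, into the relapse analysis where strata allow. With three hospitals and 40 patients in each smaller arm, the average is about 13 per centre (40/3), and relapse is defined only after recovery, so sparse strata should be checked for and a fallback stated.

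The cost is wording, plus the decision on a PASI time point, and notice to the parties listed under Protocol amendments. Both covariates are already collected. The change should be dated before the database is locked.
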